### Sample size and power

Our initial work has identified 51 656 individuals with acute MI and 58 146 with stroke in the SAIL Databank who meet all inclusion criteria. In the previous study by Smeeth *et al*,^6^ the sample size was 53 709 for acute MI, and 55 157 for stroke, where 16% of acute MI cases, and 21% of stroke cases were exposed to UTI.^6^ Based on a conservative exposure rate of 10%, and an at-risk window of 90 days, we estimated the effect size that could be reliably detected with our potential sample size, using the sample size function in the SCCS package in R. The available sample provides 90% power to detect an IRR of 1.3 at the alpha=0.05 level, which is smaller than the IRRs detected in Smeeth *et al*^6^

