**Ethics and dissemination:**

Data access, research permissions and approvals have been obtained from the SAIL independent Information Governance Review Panel, project number 0972. Findings will be disseminated through conferences, blogs, social media threads and peer-reviewed journals. Results will be of interest internationally to primary and secondary care clinicians who manage UTIs and may inform future clinical trials of preventative therapy.

STRENGTHS AND LIMITATIONS OF THIS STUDYThe self-controlled case series method controls for time-invariant confounding, enabling more reliable causal estimates of the association between urinary tract infection (UTI) and acute myocardial infarction (MI) or stroke, compared with between-individual study designs.A causal relationship between UTI and acute MI or stroke has implications for our understanding of cardiovascular disease mechanisms and may inform new methods of disease prevention.Using individual-level population-scale anonymised, routinely collected electronic health record (EHR) data provides adequate power to study subgroups and maximises representativeness and generalisability.EHR data are collected and recorded for clinical purposes, and therefore, the reliability of research findings is dependent on the quality and completeness of these data.Clinical and microbiological diagnoses of UTI are subject to caveats, and therefore, we will use several definitions of UTI that use the different data sources in the Secure Anonymised Information Linkage Databank.

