The relationship between UTIs and acute cardiovascular events is less well studied than for RTIs. Only one previous study has examined this relationship. Smeeth *et al* used the self-controlled case series (SCCS) method to analyse data from the General Practice Research Database. They found increased rates of MI and stroke subsequent to UTI, with the risk being highest in the first 3 days.^6^ However, the data analysed are almost 20 years old, and there have been no attempts to replicate the findings. Furthermore, the study defined UTI using clinical codes only, so it is unclear if the reported associations related to individuals with clinical symptoms alone, or symptoms and bacteriuria, making it difficult to interpret whether individuals had true UTIs, or whether non-specific symptoms were misdiagnosed as UTI but represented early signs of a cardiovascular event. In addition, other studies have found that roughly two-thirds of women suspected to have UTI on presentation to primary care have no evidence of UTI on microbiological culture.^20^ Therefore, the use of clinical codes alone to define UTI may lead to bias from misclassification of the exposure.

Therefore, the aim of this study is to determine whether there is a causal relationship between UTI and acute MI or stroke by analysing linked general practice, hospital admission and microbiology data, from a representative sample of the Welsh population. We will use the SCCS method, which controls for time-invariant confounding, enabling us to more reliably draw causal inferences between UTI and acute MI or stroke, compared with between-individual study designs.

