### Exposure

The exposure of interest is an UTI. The risk period is 0–90 days following an UTI. This period was chosen as previous research has shown an increase in acute MI and stroke risk in the 1–90 days following an UTI.^6^ There will be a prerisk period of 7 days before the risk period, to allow for the situation where an individual has an UTI for several days prior to consultation, so events in this period are not erroneously attributed to the baseline period. Individuals can be exposed to an UTI more than once during the observation period. Each exposure will be followed by the same 90-day risk period. Baseline periods are all other times.

To ascertain UTI, we developed definitions that reflected the Public Health Wales Microbiology Division’s standard operating procedure for the investigation of urine.^36^ These procedures are followed by NHS microbiology laboratories across Wales. For each definition, the data sources required and the clinical scenario represented is summarised in table 2, and the code lists used are given in online supplemental material B–D. In our primary analysis, an individual will be regarded as being exposed to an UTI if the following events occur within a 7-day window:

A General Practice (GP) record of an UTI diagnostic or symptom code.A GP record of an antibiotic prescription.A microbiology record of a urine sample with bacterial growth of a single organism of ≥1x10^8^ colony-forming units (CFU) per litre and white cell count (WCC)≥1x10^8^/L. If there are two organisms grown, both must demonstrate growth of ≥1x10^8^ CFU per litre. More than two organisms will be regarded as mixed growth and thus not supportive of an UTI diagnosis. In a sensitivity analysis, we will widen the microbiological criteria and include all urine samples with bacterial growth of a single organism of ≥1x10^7^ CFU per litre, irrespective of the WCC.

**Table 2 T2:** Definitions of UTI for primary and secondary analyses. As the UTI definitions are combinations of two or more components, the start of the risk period is defined as the date of the earliest component

	UTI-related read code in GP data (online supplemental material B)	Antibiotic prescription in GP data (online supplemental material C)	UTI-related ICD-10 code in PEDW (online supplemental material D)	Urine culture results in WRRS	Time frame	Clinical scenario

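### The 10% exposure rate behind the power claim is not shown to be conservative for the culture-confirmed primary definition; 90% power for an IRR of 1.3 is doubtful for MI and may be met for stroke

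*Protocol article*

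**What the plan says.** The section on sample size and power starts from the case counts: "Our initial work has identified 51 656 individuals with acute MI and 58 146 with stroke in the SAIL Databank who meet all inclusion criteria". It then cites the earlier study, "where 16% of acute MI cases, and 21% of stroke cases were exposed to UTI". The calculation is "Based on a conservative exposure rate of 10%, and an at-risk window of 90 days", and the conclusion is "The available sample provides 90% power to detect an IRR of 1.3 at the alpha=0.05 level". It does not say whether that sentence refers to MI, stroke or both, or whether alpha is two-sided.

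The Introduction describes the same earlier study as one where "the study defined UTI using clinical codes only", and it counts this as a weakness. It adds that "roughly two-thirds of women suspected to have UTI on presentation to primary care have no evidence of UTI on microbiological culture".

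The primary exposure, set out under Exposure and in Table 2, has three parts that must fall within 7 days: a GP diagnostic or symptom code, an antibiotic prescription, and a urine culture in which growth and white cells both reach set thresholds. Table 2, under secondary analysis 2, notes that some suspected UTIs are never cultured. The Statistical analysis section keeps only people with both the outcome and the exposure.

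**The concern.** In a self-controlled case series only exposed cases carry information, so the exposure share sets the effective sample size. The 10% is cautious only relative to a codes-only exposure, which the authors reject for their primary analysis. The article gives no exposure share under its own, much narrower definition.

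If the true share is well under 10%, the primary analysis has less power than stated. A reader who relies on the 90% figure could then take a null MI result as stronger evidence against an IRR of 1.3 than it is.

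**Working it through.** **Inputs.** Cases: 51,656 MI and 58,146 stroke (Sample size and power). Risk window 90 days, IRR ρ = 1.3, alpha 0.05, taken as two-sided. Mean observation by sex comes from Summary of cases and the sex split from Table 3:

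- MI: 0.628 × 3251 + 0.372 × 2981 = 3,151 days, so r = 90/3151 = 0.0286.
- Stroke: 0.494 × 2981 + 0.506 × 2796 = 2,887 days, so r = 90/2887 = 0.0312.

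**Formula.** Signed-root likelihood-ratio sample size for the self-controlled case series, without age effects. This is assumed to be the method behind the package function that the article names.

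- π = ρr / (ρr + 1 − r)
- A = 2[π ln ρ − ln(ρr + 1 − r)]
- B = (ln ρ)² π(1 − π) / A
- exposed cases needed = (1.960 + 1.282√B)² / A
- power = Φ[(√(nA) − 1.960) / √B], with n the number of exposed cases

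MI: π = 0.0368, A = 0.002254, B = 1.083. Stroke: π = 0.0401, A = 0.002450, B = 1.082.

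**The article's own figure.** At 10% there are 5,166 exposed MI cases and 5,815 exposed stroke cases. Power is 92% and 96%. The stated 90% therefore follows from the 10%, and the arithmetic is not in dispute. (If everyone were observed for the full 4,018-day study period, 10% would give 85% and 89%. The article's own mean observation times are shorter and are used here.)

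**Exposure needed for 90% power.**

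- MI: 4,813 exposed cases; 4,813 / 51,656 = 9.3%, which is 58% of the earlier 16%.
- Stroke: 4,426 exposed cases; 4,426 / 58,146 = 7.6%, which is 36% of the earlier 21%.

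So MI has almost no slack below 10%, while stroke has some.

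**Applying the article's one-third confirmation, one episode per person.**

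- MI: 16% / 3 = 5.3%, about 2,755 exposed cases, power 70%, IRR detectable with 90% power 1.40.
- Stroke: 21% / 3 = 7.0%, about 4,070 exposed cases, power 87.5%, detectable IRR 1.31.

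**Allowing for repeat episodes.** Suppose each exposed person has k suspected episodes, each confirmed with probability 1/3. The share with at least one confirmed episode is then the earlier share × [1 − (2/3)^k]. The lower power figure counts one 90-day window per person; the higher counts every confirmed window.

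| k | MI share | MI power | Stroke share | Stroke power |
|---|---|---|---|---|
| 1 | 5.3% | 70% | 7.0% | 87.5% |
| 1.5 | 7.3% | 82–85% | 9.6% | 95–97% |
| 2 | 8.9% | 89–93% | 11.7% | 98–99% |

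**Allowing for lost episodes.** Missing cultures, the white-cell criterion and the 7-day rule lower the confirmed fraction by an amount the article does not give. With an assumed 20% confirmed and k = 2, MI power is 73–77% and stroke power 90–92%.

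**The case against.** The strongest objection is a mismatch of units. The 16% and 21% are shares of people; the one-third is a fraction of suspected episodes, and it comes from women in primary care, whereas 63% of MI cases here are male. Repeat UTIs are expressly allowed under Study design, and the Introduction reports 37% of women with at least one and 29% with more than one. With two suspected episodes per exposed person, all cultured, the 90% claim roughly holds for MI and holds easily for stroke. This stands. A reader might infer that the stated power is simply not delivered; the documents do not support that, because they give neither the number of suspected episodes per person nor the proportion cultured. The two push in opposite directions.

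The article also claims that the data source "provides adequate power to study subgroups", and it will report windows as short as 1–7 days. A reader might infer that the primary calculation is at fault for not covering these. It is not: the primary hypothesis and the calculation both use 90 days, and a condensed article need not print each subgroup calculation.

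Finally, the sample is every eligible case in a fixed databank, so no recruitment decision turns on this figure, and the 95% confidence intervals will show what is excluded. That limits the harm. It does not make the label conservative correct.

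**Conclusion.** The point stands as an unsupported planning input, not as an arithmetic error. The 10% is benchmarked on a looser exposure than the one being powered, and the article's own confirmation figure points below it. For MI the claim is doubtful: it needs 9.3% exposed, and power is about 70% at one confirmed third with one episode per person, 82–85% at 1.5 episodes and 89–93% at 2. For stroke the shortfall is marginal in the one-episode case (87.5% against 90%) and disappears with modest repetition, unless many episodes go uncultured. These figures assume a two-sided 0.05 level, no age effects, the mean observation times in the article, and exposure shares like those of the earlier study. Only the actual count under the primary definition can settle the matter.

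**What to change.** Count the MI cases and the stroke cases with at least one UTI under the primary definition, without looking at when the UTI fell relative to the event. From those counts, restate the IRR detectable with 90% power over 90 days, separately for MI and stroke, and state whether alpha is two-sided.

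Until the count is available, remove the word conservative and give power across a stated range of assumed exposure, for example 5–10%. By the formula above, that range gives 67% to 92% for MI and 75% to 96% for stroke.

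The cost is one count in data already held, and possibly a less favourable figure. The design and the analysis do not change.

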### Patient and public involvement

We developed this research proposal in collaboration with members of the Wales Centre for Primary and Emergency Care Research Service Users group (SUPER). We have a patient and public involvement (PPI) plan and are consulting the SAIL consumer panel and SUPER regarding all stages of this research, including ongoing discussion of analysis plans, review of findings, and plans for dissemination (eg, public facing outputs). We have extended our sub-group analysis to include individuals with diabetes in response to discussions with the SAIL consumer panel members. Identifying PPI for future stages of this research is a secondary objective of our PPI plan.

### Summary of cases

The individuals with an ICD-10 code for either MI or stroke were selected according to the eligibility criteria, as shown in figure 2. There are 58 146 individuals with an ICD-10 code for stroke, and 51 656 individuals with an ICD-10 code for MI, a total of 105 930 unique individuals (it is possible for an individual to be in both the stroke and the MI group). Stroke cases were 49% male, MI cases 63% male. Female stroke cases were older than males, with a median age of 79 years (25–75th centiles 69–87) compared with a median of 74 years (25–75th centiles 64–82) for males. Female MI cases were also older, with a median age of 77 (25–75th centiles 66–85) compared with 69 (25–75th centiles 59–78) for males.

**Figure 2 F2:**
[figure not shown]
Case selection process. *Individuals appear and are counted in both the stroke and MI datasets if they had both an MI and a stroke event within the study period. MI, myocardial infarction; PEDW, Patient Episode Database for Wales; SAIL, Secure Anonymised Information Linkage; WLGP, Welsh Longitudinal General Practice data; WDSD, Welsh Deographic Service Dataset.

The mean length of observation (study entry to study exit) of stroke cases was 2796 days for females and 2981 days for males. For MI cases, 2981 for females and 3251 for males. History of diagnoses and prescription drugs is taken from all health records available for each individual. Health data is available for a median of 13 years (25–75th centiles 8–16) prior to the study start.

Characteristics of cases, including a history of diagnoses and prescription drugs prior to an event, smoking status, Welsh Index of Multiple Deprivation version 2019 and electronic Frailty Index are given in table 3.

**Table 3 T3:** Characteristics of cases of stroke and MI

Characteristic	Stroke	MI
Sex (% male)	49.4	62.8
Age of males (mean (25th, 75th centiles))	74 (64, 82)	69 (59, 78)
Age of females (mean (25th, 75th centiles))	79 (69, 87)	77 (66, 85)
Welsh Index of Multiple Deprivation (WIMD) 2019 quintiles*		
1 (least deprived)	19.8	20.6
2	20.8	20.5
3	20.3	20.9
4	20.4	20.1
5 (most deprived)	18.6	17.9
Current smoker (%)	19.8	24.2
electronic Frailty Index (mean (SD))	0.16 (0.12)	0.15 (0.12)
Prescribed lipid-lowering drugs (%)	49.0	49.6
Prescribed aspirin (%)	43.7	41.3
Prescribed hypertensive drugs (%)	59.1	55.1
Prescribed beta blockers (%)	39.6	37.3
Chronic kidney disease (%)	20.9	18.9
COPD (%)	9.9	10.9
Asthma (%)	15.1	16.0
Hypertension (%)	51.2	46.2
Diabetes (%)	19.4	20.7
Cardiovascular disease (%)	56.4	53.4
Coronary Heart Disease (%)	15.9	21.5
Atrial fibrillation (%)	16.0	8.7
Heart failure (%)	8.4	8.6
Peripheral vascular disease (%)	7.2	7.7
Angina (%)	11.3	16.0
Transient ischaemic attacks (%)	9.4	5.0
Total no of cases	58 150	51 659

*LSOA version 2011 and WIMD version 2019

COPD, Chronic Obstructive Pulmonary Disease; LSOA, Lower Super Output Area; MI, myocardial infarction.

### Ethics and dissemination

All study data will be held within the SAIL Databank, an ISO27001 certified TRE for anonymised individual-level data. Data access, research permissions and approvals have been obtained from the SAIL independent IGRP, project number 0972. Analyses will be conducted within the SAIL TRE. There are strict disclosure control processes in place. Only aggregated outputs will be approved for release to ensure individuals are not identified. Findings will be disseminated through peer-review journals and conferences. Results will be of interest internationally to primary and secondary care clinicians who manage UTIs. An association between UTI and either MI or stroke will support a future funding application for a randomised trial of preventative treatments, such as antiplatelet drugs.
